## 2.5 Procedure

Participant allocation will be carried out using a computer-generated randomisation sequence through Random Allocation Software 2.0, which will assign caregivers to either the mind-mindedness (MM) training intervention group (n=50) or the peer support control group (n=50). The randomisation will be stratified by country (UK and Iran) to maintain a balanced allocation within each cultural context (FIGURE

1).

Data collection will take place at three time points: baseline (T0), post-intervention (T1), and 3-month follow-up (T2). At each time point, data will be collected through validated caregiver-report measures (FIGURE

2). Mind-mindedness will be assessed using the Mind-Mindedness Coding Manual 2.2 (64), which offers a structured framework for coding caregivers' descriptions of their children. This method evaluates both the frequency and appropriateness of the mental-state language caregivers use when describing their child. It has been widely applied in developmental studies involving preschool-aged children. Child social anxiety symptoms will be measured using the Spence Children’s Anxiety Scale – Parent Version (SCAS-P)(65), while the scale was initially validated for children aged 6 to 12, it has also been effectively used in parent-report studies with younger children aged 4 to 6(66). Attachment security will be assessed using the Attachment Insecurity Screening Inventory (AISI) for Preschoolers (67). This caregiver-report tool is specifically designed for two age groups: children aged 2 to 5 years and 6 to 12 years old, which evaluates both anxious and avoidant attachment patterns. The AISI has demonstrated good construct validity and cross-cultural applicability, making it suitable for use in both the UK and Iranian populations.

The assessment of Theory of Mind (ToM) will be conducted using the Theory of Mind Task Battery (68) for evaluating the theory of mind. The battery has been validated for use with preschool children and demonstrates strong convergent validity with other socio-cognitive measures. All measures were selected based on their age appropriateness, prior validation within preschool populations, and their cross-cultural applicability.

Additionally, demographic information (such as age, gender, socio-economic status, and cultural background) will be collected to describe the study population and control for potential confounding variables. Programme adherence will be monitored through attendance records and weekly caregiver reflections on their experiences.

The informed consent process will follow institutional guidelines, ensuring participants receive detailed study information in their preferred language (English or Persian). Participants will have opportunities to ask questions and will receive a clear explanation of their right to withdraw from the study. The Principal Investigator (PI) is responsible for obtaining informed consent from all potential trial participants.

To enhance engagement in the online format, participants will receive regular reminders via email and SMS before each session. The sessions will be interactive and will include breakout room role-plays and guided reflection activities. The control group will encourage informal peer support and provide a platform for them to share their experiences.

Comprehensive data protection measures will be implemented, including secure storage of consent forms and assessment data in encrypted, password-protected files. Unique participant identifiers will be assigned, and access will be restricted to authorised research personnel only. All data management procedures will comply with GDPR and local data protection regulations. The final dataset will be accessible only to the research team and will be stored according to Heriot-Watt University's data retention policy. This thorough approach to randomisation, data collection, and protection ensures both scientific validity and participant confidentiality throughout the study.

Figure 2-2."Participants’ Timeline"

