## 2.4 Participants

The study aims to recruit 100 primary caregivers (aged 18-60 years) of preschool-aged children (aged 4-7 years) who exhibit symptoms of social anxiety. Eligible participants must reside in either the United Kingdom or Iran. Caregivers whose children have existing clinical diagnoses or are currently receiving other forms of treatment or support will not be included in the study. Children will be included in the study based on symptoms of social anxiety reported by caregivers, assessed using the Spence Children’s Anxiety Scale – Parent Version (SCAS-P). Although the SCAS was initially validated for children aged 6 to 12 (63),it has been reliably utilised with younger children aged 4 to 6 in parent-report studies (Edwards et al., 2010). For this study, the inclusion criteria will specifically focus on elevated scores in the social phobia subscale. Those whose anxiety profiles indicate separation anxiety or general behavioural inhibition, rather than social anxiety, will be excluded during the screening process. Children with a confirmed clinical diagnosis, such as autism spectrum disorder, generalised anxiety disorder, or ADHD, along with those currently receiving psychological or educational treatment, will not be eligible for participation. The research team will not make any formal diagnoses; inclusion decisions will be based solely on parent-reported data obtained through the SCAS-P. This approach guarantees consistency across participants while focusing on observable symptoms rather than clinical labels.

Participants will be recruited through a combination of targeted outreach and community engagement strategies. This includes advertisements in preschools and nurseries, referrals from early years professionals, and word-of-mouth recommendations from other caregivers. The recruitment strategy is designed to ensure a demographically diverse yet diagnostically homogeneous sample of families, with equal representation from the UK and Iran.

Due to the nature of the intervention, participant blinding is not possible, as caregivers will be fully informed of their group allocation, either participating in mind-mindedness training sessions or joining a peer-support group. However, the assessors responsible for data collection and analysis, including those evaluating mind-mindedness, child social anxiety, attachment, and theory of mind, will remain blinded to the group allocations to ensure an unbiased evaluation of outcomes.

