## 2.8 Statistical methods

### 2.*8*.1 Sample Size and Power

A power analysis was conducted in advance using G*Power 3.1 to determine the necessary sample size for linear regression models with two predictors: group assignment and baseline score. Assuming a medium effect size (f² = 0.15), an alpha level of 0.05, and a power of 0.80, the analysis indicated that a minimum sample size of 89 participants is required. To account for an expected attrition rate of approximately 10–15%, we plan to recruit 100 participants, with 50 participants in each group. These participants will be evenly distributed between the United Kingdom and Iran. This target is deemed feasible and suitable for an early-phase efficacy trial. The sample is designed to provide sufficient power for testing the primary effects of the intervention using regression-based methods, while maintaining enough power for within-group analyses.

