### 2.*8*.2 Primary Analysis

The primary analysis will evaluate the effectiveness of the mind-mindedness training in improving outcomes for both caregivers and children immediately after the intervention. We will use linear regression models for each outcome, which includes caregiver mind-mindedness, child social anxiety (using SCAS-P), attachment insecurity (AISI), caregivers’ MM, and the Theory of Mind (ToM Task Battery). Each model will compare the post-intervention scores (Time 1) between the intervention and control groups, while controlling for baseline values (Time 0). All analyses will adhere to intention-to-treat principles. The effects of the intervention will be assessed using linear regression models, comparing outcomes at post-intervention (T1) and follow-up (T2) to baseline (T0), while controlling for baseline scores. When applicable, multiple imputation with 20 datasets will be used to address any missing data. Effect sizes will be reported using standardised beta coefficients and 95% confidence intervals.

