### 2.*8*.4 Data Management

Data will be collected electronically using REDCap, ensuring standardised collection and secure storage. Quality assurance measures will include double data entry verification for 20% of cases, automated range checks, weekly backups, and monthly data integrity audits to identify patterns of missing data. All analyses will be conducted using Stata 17.0 (StataCorp, College Station, TX) with a significance level of p < 0.05 (two-tailed). Results will be reported following CONSORT guidelines for randomised trials.

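### Section 2.5 promises demographic control of confounding that no stated model carries out; the non-randomised mediator-to-anxiety path is left open to confounding by child age

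*Protocol*

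**What the plan says.** Section 2.5 (Procedure) lists "demographic information (such as age, gender, socio-economic status, and cultural background" and says that it "will be collected to describe the study population and control for potential confounding variables". The list is open-ended and does not say whether age means the child's or the caregiver's. Section 2.4 admits "preschool-aged children (aged 4-7 years".

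The statistical section is more specific:

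- 2.8.1 sizes the trial for "linear regression models with two predictors: group assignment and baseline score".
- 2.8.2 compares the arms at T1 "while controlling for baseline values (Time 0".
- 2.8.3 repeats this at T2, again with the baseline value as the only covariate.
- The path analysis in 2.8.3, with attachment and theory of mind as mediators of the effect of training on anxiety, names fit indices but no covariate.
- The moderation models in 2.8.3 add country (UK or Iran) interaction terms.

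Country is therefore the only element related to the demographic list that enters any stated model. Age, gender and socio-economic status enter none.

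**The concern.** The two parts of the protocol do not match. Section 2.5 gives a purpose that the models do not fulfil. If it were acted on later, covariates would be picked from an open list after the data are in, across several outcomes.

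The consequence differs by analysis. For the arm comparison, randomisation removes confounding, so leaving out child age can only cost precision. For mediation, only the path from arm to mediator is randomised. The path from mediator to anxiety is observational, and child age is an obvious candidate common cause. The protocol treats theory of mind as developing in these years and describes some early anxiety as a normal part of development. Its attachment inventory has separate versions for ages 2 to 5 and 6 to 12, and the sample straddles them. Mediation is a secondary analysis, but the Discussion part of the abstract and the Introduction make it the trial's explanation of how training works, so a confounded path would affect a central interpretation.

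**Working it through.** **1. The plan's own figure.** Inputs from 2.8.1 and 2.8.4: "Assuming a medium effect size (f² = 0.15), an alpha level of 0.05, and a power of 0.80", two-sided, two predictors. With the noncentral F distribution, λ = f² × N and N − predictors − 1 denominator degrees of freedom, the required N at 80% power is 55 for the group coefficient and 68 for the joint test of both predictors. The stated 89 does not reproduce at 80%; it matches the group coefficient at 95% power. That is a separate matter. What counts here is the price of one more covariate at f² = 0.15: at N = 100, power for the group coefficient is 96.96% with two predictors and 96.95% with three. A useless covariate costs less than 0.1 point.

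**2. Precision of the arm effect.** The protocol gives no correlation of age with any outcome, so these are assumptions. Let ρ be the correlation of age with the true score, rel the reliability of the baseline score, and the true score stable, so that the T0–T1 correlation equals rel. Then

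- r_a = ρ × √rel
- partial r (age with T1, given T0) = (r_a − rel × r_a) / √[(1 − rel²)(1 − r_a²)]
- SE ratio with age added, N = 100: √[(1 − r²) × 97/96]

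| Outcome (assumed) | ρ | rel | partial r | r² | SE ratio |
|---|---|---|---|---|---|
| Theory of mind, low | 0.4 | 0.8 | 0.13 | 0.016 | 0.997 |
| Theory of mind, high | 0.6 | 0.6 | 0.26 | 0.069 | 0.970 |
| Anxiety, low | 0.2 | 0.8 | 0.06 | 0.004 | 1.003 |
| Anxiety, high | 0.3 | 0.6 | 0.12 | 0.014 | 0.998 |

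So age explains about 2% to 7% of residual variance for theory of mind and about 0.4% to 1.4% for anxiety. The lost degree of freedom costs about 1% (97/96 = 1.010), which cancels most or all of the gain for anxiety.

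**3. Confounding of the theory-of-mind-to-anxiety path.** Simulation with N = 100, 4,000 replicates, a true path of zero, arm in the model and an assumed T0–T1 correlation of 0.7 for each measure. Let a be the correlation of age with theory of mind and c that of age with anxiety. With no covariates the expected spurious coefficient is 0.7 × a × c. For a = 0.7 and c = 0.3 this is 0.7 × 0.7 × 0.3 = 0.147, as simulated.

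| a | c | no covariates: coefficient, type I error | baseline anxiety | both baselines | age |
|---|---|---|---|---|---|
| 0.3 | 0.2 | 0.043, 6.7% | 0.014, 5.2% | 0.010, 4.8% | 0.001, 4.8% |
| 0.3 | 0.3 | 0.063, 8.9% | 0.020, 6.0% | 0.013, 5.0% | 0.001, 5.1% |
| 0.5 | 0.2 | 0.069, 11.1% | 0.019, 5.8% | 0.011, 4.4% | −0.001, 5.2% |
| 0.5 | 0.3 | 0.105, 18.0% | 0.031, 6.6% | 0.019, 4.9% | −0.001, 5.2% |
| 0.7 | 0.2 | 0.096, 15.7% | 0.029, 6.6% | 0.020, 5.2% | −0.003, 5.3% |
| 0.7 | 0.3 | 0.147, 30.4% | 0.046, 9.3% | 0.026, 5.8% | −0.002, 4.6% |

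With c = 0 the coefficient is about zero and type I error about 5% in every column. The simulation error of a 5% rate is √(0.05 × 0.95 / 4000) = 0.34 points, so differences of half a point should not be read. The baseline scores do much of the work; age removes the remaining coefficient.

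**The case against.** Several points on the other side stand.

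- A full covariate list is commonly left to the analysis plan, which is not at hand, and the regressions say that they control for baseline without saying that they control for nothing else. This limits the point to the mismatch and its consequence. It does not remove it, because 2.8.1 counts the predictors.
- It would be wrong to say that every stated model adjusts for baseline alone. The moderation models contain country, and the path model states no covariate at all. Only the T1 and T2 regressions fit that description.
- A reader might infer that the arm effect is biased or seriously weakened. Randomisation rules out the first, and the second table row pair for anxiety shows that the precision at stake there is close to nil.
- A reader might take assumed correlations of 0.6 and 0.3, multiply them to 0.18, and conclude that a false path would be significant in about 4 of 10 samples of 88 (Fisher z 0.182 × √85 = 1.68, power about 0.39). That is a raw two-variable correlation that ignores measurement error and any baseline adjustment. The protocol supplies neither correlation, and the simulated rates are lower.
- A confounded mediator-to-anxiety path does not by itself produce mediation; training must also change the mediator, and that path is randomised.
- The sign is unknown. If older children score higher on both measures, the induced association is positive and would hide the hypothesised protective path.
- Gender and socio-economic status could confound the same path. Child age is singled out because of the 4 to 7 year range and the developmental nature of the measures; the protocol contains no evidence that ranks these variables.

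**Conclusion.** The point holds in a limited form. The promise in 2.5 is not carried out by the T1, T2 or path models. The effect on the randomised comparison is small: no bias, and a standard error for theory of mind that could be about 0.3% to 3% smaller with age, with essentially no change for anxiety. The effect on the mediator-to-anxiety path can be material if the path model is fitted as written, with type I error of about 7% to 30% for a true path of zero. It falls to 5% to 9% with baseline anxiety and to about 5% with age.

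All of these sizes rest on assumed correlations and stability, and the confounding arises only if age relates to anxiety as well as to theory of mind. The protocol shows that the path is unprotected; it does not show that a false mechanism will be reported. The change is cheap and worth making before the data are analysed.

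**What to change.** - **2.8.3, path model:** include child age at T0 and the baseline scores of the mediator and of anxiety in both the mediator and the outcome equations.
- **2.8.2 and 2.8.3, T1 and T2 regressions:** add child age at T0 as a prespecified linear covariate. The benefit is chiefly for theory of mind.
- **2.8.1:** bring the stated number of predictors into line with the models.
- **2.5:** replace the open wording on confounding with these named covariates, and say that age means the child's age. Keep country for the planned UK–Iran moderation analysis; it must not be reduced to a descriptive variable.

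The cost is one degree of freedom per model for age, plus the baseline terms in the path model. Exact child age must be recorded at T0; the protocol documents only the 4 to 7 year eligibility band, so the data form should be checked.

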All three sessions will include video examples demonstrating effective and ineffective approaches, as well as role-play exercises where caregivers can practice these techniques with guided feedback. The role-plays will be led by trained child psychologists. They will give immediate feedback and answer questions to ensure that caregivers are effectively practising mentalizing caregiving. Throughout the training, caregivers will receive support materials and reminders to track their progress and reflections. Participation will be tracked through attendance records and the completion of reflection activities to make sure that participants are following the programme guidelines.

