## 2.7 Control group

The peer support (control) group will access a private online group for the exchange of experiences and coping strategies related to the child's anxiety, without direct MM training. Control group participants will access a secure online forum, where they can post entries and interact through comments, called Padlet. No Zoom sessions will be used, and no structured training or psychoeducation will be delivered in this group.

The comprehensive set of measures includes assessments of MM, child anxiety scales, and evaluations of attachment and theory of mind. Measures of MM will be coded from caregiver descriptions of the child using the MM Coding Manual 2.2 (64). Child anxiety will be assessed with the Spence Children’s Anxiety Scale (65). Attachment will be measured using the Attachment Insecurity Screening Inventory (67). Theory of mind will utilise the Theory of Mind Task Battery (69). The three-day MM training programme incorporates psychoeducation, role-play exercises, and practical sessions, while the peer support (control) group serves as an active control condition.

Fig 1-2. RCT design

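### Training appears to be given in shared Zoom sessions, but the planned regression ignores clustering; if outcomes correlate within session groups, intervals are too narrow and type I error exceeds 5%

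*Protocol*

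**What the plan says.** Section 2.5 randomises individual caregivers, 50 to each arm, stratified by country. For the training arm it says "The sessions will be interactive and will include breakout room role-plays and guided reflection activities". Section 2.6 describes three one-hour Zoom sessions, with role-play in every session and reflective discussion in the last. It adds "The role-plays will be led by trained child psychologists", with feedback given on the spot. Controls have no sessions. Section 2.7 gives them an online forum where "they can post entries and interact through comments".

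Section 2.8.1 sizes the trial for "linear regression models with two predictors: group assignment and baseline score". It uses these inputs: "Assuming a medium effect size (f² = 0.15), an alpha level of 0.05, and a power of 0.80". It concludes that "a minimum sample size of 89 participants is required". Section 2.8.2 says "The effects of the intervention will be assessed using linear regression models", adjusted for the baseline score. The protocol mentions no session-group or facilitator term, cluster-robust variance, ICC or design effect. It does not give the number or size of training groups, or the number of psychologists.

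**The concern.** A breakout room divides a shared meeting, so the natural reading is that trained caregivers learn together while controls do not attend sessions at all. That is a partially nested design. If some groups or psychologists do better than others, the outcomes of caregivers who share them are correlated, and 50 trained caregivers carry less information than 50 independent ones. A regression with only arm and baseline treats them as independent and takes no account of this. At stake are the coverage of the 95% confidence intervals and the error rate of the arm comparison. An effect that reflects a few good or poor training groups could be reported as an effect of the programme.

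**Working it through.** **Inputs from the protocol.** 50 caregivers per arm, evenly split by country, so about 25 per arm per country (2.5, 2.8.1). Two-sided 5% test (2.8.4). f² = 0.15, power 0.80, two predictors, minimum 89 participants, 10-15% attrition (2.8.1).

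**Assumptions, because the protocol gives no figure.** Training groups of size m = 8, 10 or 25, where 25 is one group per country. ICC of 0.01, 0.05 or 0.10 on the baseline-adjusted scale. Controls independent in the main calculation.

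**The plan's own figure.** The noncentral F calculation with λ = f²·N and N − 3 denominator degrees of freedom does not return 89 at 80% power. It gives 55 for the arm coefficient and 68 for the joint test of both predictors. For the arm coefficient, 89 corresponds to 95% power. This is a separate matter, but it shows that 89 contains no hidden allowance for clustering that the text explains.

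**Effect on the test.** With clustering in one arm only, the design effect in that arm is 1 + (m − 1)·ICC. The variance of the arm difference grows by

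ratio = [2 + (m − 1)·ICC] / 2

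and the true type I error of the nominal 5% test is 2·[1 − Φ(1.96/√ratio)].

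Example, m = 10 and ICC 0.05: ratio = (2 + 9 × 0.05)/2 = 1.225; √1.225 = 1.107; 1.96/1.107 = 1.77; type I error 7.7%, so interval coverage is 92.3%.

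| m | ICC | Variance ratio | SE factor | Type I error |
|---|---|---|---|---|
| any | 0 | 1.000 | 1.000 | 5.0% |
| 8 | 0.01 | 1.035 | 1.017 | 5.4% |
| 10 | 0.01 | 1.045 | 1.022 | 5.5% |
| 8 | 0.05 | 1.175 | 1.084 | 7.1% |
| 10 | 0.05 | 1.225 | 1.107 | 7.7% |
| 8 | 0.10 | 1.350 | 1.162 | 9.2% |
| 10 | 0.10 | 1.450 | 1.204 | 10.4% |
| 25 | 0.01 | 1.120 | 1.058 | 6.4% |
| 25 | 0.05 | 1.600 | 1.265 | 12.1% |
| 25 | 0.10 | 2.200 | 1.483 | 18.6% |

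A simulation of the planned regression (50 per arm, 20,000 runs per scenario) agrees: 7.8% for m = 10 and 12.0% for m = 25 at ICC 0.05.

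**Control forum.** Suppose each country has one forum of 25 users and both arms have ICC 0.05. The ratio is then the mean of the two design effects. For training groups of 10 this is (1.45 + 2.20)/2 = 1.825, and the type I error is 14.7%. Across training groups of 5 to 25 it runs from 13.3% to 18.6%.

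**Power with the corrected variance.** Take f² = 0.15 on the arm coefficient and 85 completers (100 less 15%), so λ = 0.15 × 85 = 12.75 divided by the ratio. Power is 0.94 without clustering. At ICC 0.05 it is 0.89 for m = 10 and 0.80 for m = 25. At ICC 0.10 with m = 25 it is 0.66. These values keep N − 3 degrees of freedom, so they are too favourable when there are few groups.

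**The case against.** **The inflation is not a fact about this trial.** A reader might infer that the type I error does exceed 5%. The protocol does not support that, since it gives neither ICC nor group size, and at ICC 0 nothing is lost. If training affected no caregiver at all, sharing a session would by itself create no correlation, and the plain test would stay near 5%. Inflation needs real differences between groups or facilitators. This stands, and the conclusion is worded conditionally.

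**The delivery is partly inferred.** A reader might also infer fixed groups run throughout by one psychologist. Section 2.6 says only that psychologists lead the role-plays. No section says that membership stays constant over the three weeks, and section 2.4 offers flexible scheduling. This stands as a limit on the assumed structure. One-to-one delivery, however, is hard to reconcile with breakout rooms.

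**The variance estimator could be left to the statistical analysis plan.** The protocol does not exclude cluster-robust errors. But it does fix the model and its two predictors, and that model does not fit the delivery it describes. A later plan can repair this only if group membership was recorded. Attendance records are planned, but recording of group or psychologist is not stated.

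**Exposure is incomplete.** Caregivers who do not attend share no group experience, so the design effect may be smaller than in the table. This stands. It lowers the figures without changing their direction.

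**A clustered model may not work.** With one group per country there are two clusters in the training arm, each aliased with country, and a random intercept is barely estimable. This stands and shapes the fix.

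**Conclusion.** The point holds in conditional form. The stated analysis makes no allowance for the shared delivery that the protocol describes. Any positive correlation within session groups or facilitators makes the intervals too narrow and pushes the type I error above 5%. With clustering in the training arm only, the excess is trivial at ICC 0.01 with groups of 8-10, about two to three percentage points at ICC 0.05 with the same groups, and about seven points at ICC 0.05 with groups of 25. Every one of these figures rests on assumed group sizes and ICCs. Correlation among forum users would add to them.

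The main harm is to coverage and error rate. It would be tempting to conclude that the trial is underpowered, but the figures do not show that in general: under the protocol's own effect size, power stays near or above 80% except with very large groups and a high ICC, or where few groups leave few degrees of freedom.

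**What to change.** - State the planned number and size of training groups and the number of psychologists, and say whether membership is fixed across the three sessions.
- Record identifiers for session group, psychologist and control forum.
- Replace the plain regression in section 2.8.2 with a partially nested mixed model: a random intercept for session group in the training arm, baseline score and country as covariates, and small-sample degrees of freedom. Kenward-Roger is available in Stata 17. Say how this combines with the 20 imputed datasets.
- If there are too few groups to estimate the group variance, report instead a sensitivity analysis that rescales the standard error over an assumed ICC range, including possible correlation among control-forum users.
- State in section 2.8.1 that the sample size assumes no clustering, and give power over the same ICC range.

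The identifiers and the change of model cost little. The price is wider intervals and lower stated power, and this could be substantial if there are only one or two groups per country. Nothing here requires a change in how the training is delivered. Running more, smaller groups would be a separate decision and could need more psychologist time.
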